### **3.6. Outcome Measures**

Assessments will be conducted at baseline (pre-treatment) and after eight weeks of rehabilitation.

Primary Outcome Measure:

- Cobb angle will be assessed using supine spinal X-ray.

Secondary Outcome Measures:

- The basal upper-lower chest wall ratio will be evaluated using chest X-ray.
- Supine Angle of Trunk Rotation (SATRL and SATRU) will be measured using a scoliometer.
- Motor function will be assessed using the CHOP INTEND scale.
- Respiratory rate and SpO2 will be measured using pulse oximetry.
- Satisfaction with orthosis use will be evaluated using the QUEST 2.0 questionnaire.

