##### Exclusion Criteria:

- Acute respiratory failure or mechanical ventilation dependency.
- Previous spinal surgery.
- Additional neurological or orthopedic disorders.
- Poor adherence to spinal orthosis or exercise protocols.

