#### 3.5. Intervention Details

##### 3.5.1. Group 1:

Participants will receive an individualized trunk exercise (ITE) program along with standard pulmonary care (PC) and pulmonary rehabilitation (IPR). Exercises will be performed daily for 8 weeks, under weekly clinical supervision.

Exercises include:

- Passive and active-assisted trunk mobilization exercises.
- Core stability training through guided postural activities.
- Supine and side-lying activities to enhance trunk control.
- Gentle active resistance exercises for trunk muscles.
- Breathing exercises to enhance diaphragmatic movement.

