### **3.5.2. Group 2:**

- Participants will receive the same intervention as Group 1, with the addition of a customized thoracolumbosacral orthosis (TLSO) worn for at least 8 hours daily.

The TLSO will feature:

- An anterior window for diaphragmatic breathing.
- Lateral modifications to facilitate chest expansion.
- Soft inner padding for enhanced comfort.
- Adjustable straps to optimize spinal alignment without over-restricting movement.

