## 5. Dissemination Plan

Findings will be disseminated through peer-reviewed journal publications, conference presentations, and clinical practice guidelines for physiotherapists managing Type 1 SMA.

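### No adverse-event or device-intolerance recording is specified, and an undated adherence exclusion could remove children who cannot tolerate the orthosis before the only follow-up

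*Protocol*

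**What the plan says.** Section 3.6 sets two assessment times: "Assessments will be conducted at baseline (pre-treatment) and after eight weeks of rehabilitation". The primary outcome is the Cobb angle. The secondary outcomes are the chest wall ratio, the supine trunk rotation angles, CHOP INTEND, respiratory rate and SpO2, and orthosis satisfaction. For the respiratory readings it says that they "will be measured using pulse oximetry". For the device it says: "Satisfaction with orthosis use will be evaluated using the QUEST 2.0 questionnaire".

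Section 3.5.2 gives Group 2 the Group 1 programme "with the addition of a customized thoracolumbosacral orthosis (TLSO) worn for at least 8 hours daily". The listed design features include "An anterior window for diaphragmatic breathing", lateral changes to allow chest expansion, and padding for comfort.

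Section 3.5.1, which applies to both groups, provides a contact between the two assessments: "Exercises will be performed daily for 8 weeks, under weekly clinical supervision". It does not say that anything is recorded there.

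The exclusion criteria in section 3.3 include "Poor adherence to spinal orthosis or exercise protocols", with no timing. Section 3.7 allows for 30% dropout and recruits 24 children. Section 4 anticipates better respiratory function with the orthosis. Section 5 names among its outputs "clinical practice guidelines for physiotherapists managing Type 1 SMA".

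No section mentions adverse events, skin or pressure problems, respiratory events, or the recording of reasons for stopping.

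**The concern.** The children are aged 2 to 6 and, by the introduction's account of the disease, have weak intercostal muscles and a paradoxical breathing pattern. Group 2 wears a trunk orthosis for many hours a day. The window and lateral modifications show that room to breathe was considered when the device was designed. Skin and breathing problems are therefore foreseeable, yet the protocol provides nowhere to record them.

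Two consequences follow.

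- **Safety information.** A problem that comes and goes between baseline and week 8, or that leads a child to leave, is not collected. An analysis plan, if one exists, cannot recover events that were never recorded.
- **The week-8 comparison.** If children who tolerate the orthosis badly are removed as non-adherent, the Group 2 readings at week 8 come disproportionately from those who tolerate it well.

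A trial meant to inform practice guidelines would then have an incomplete account of harm to set against any benefit.

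**Working it through.** The protocol gives no figure for harm or intolerance, so the check is mainly a comparison of sections. The arithmetic only gives scale.

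**1. What each measure can detect**

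| Measure in 3.6 | Can show | Cannot show |
|---|---|---|
| Respiratory rate, SpO2 | Worsening still present at week 8 in a child who attends | Episodes between visits; anything in a child who has left |
| QUEST 2.0 | Satisfaction with the device | Skin or breathing events; reasons for interruption |
| Chest wall ratio, CHOP INTEND | Structural or motor worsening at week 8 | Acute events |

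No item records events, interruptions or reasons.

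**2. When the adherence exclusion can operate**

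- Only Group 2 receives the study orthosis (3.1, 3.5.2).
- No run-in with the orthosis is described before randomisation.
- Adherence to the study orthosis can therefore be observed only after allocation, and only in Group 2.
- The exercise part of the criterion can apply to both groups.
- The criterion stands under participant selection and carries no date. Removal after randomisation is thus possible but not stated.

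**3. How many children could be affected**

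- Section 3.7: 18 × 1.30 = 23.4, rounded up to 24. This reproduces the recruited number.
- Equal allocation (assumed, in line with the stated minimum of 9 per group): 24 / 2 = 12 per arm.
- The protocol's own dropout allowance: 0.30 × 12 = 3.6, so about 3 to 4 children per arm could leave, with no stated record of why.

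**4. Could an arm this small show anything if events were recorded?**

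The probability of at least one event is 1 − (1 − r)^n, where r is an assumed true rate.

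| r (assumed) | n = 12 | n = 9 |
|---|---|---|
| 10% | 1 − 0.9^12 = 0.718 | 1 − 0.9^9 = 0.613 |
| 20% | 1 − 0.8^12 = 0.931 | 1 − 0.8^9 = 0.866 |

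If events were recorded and none occurred in 12 children, the upper 95% limit for the rate would be 1 − 0.05^(1/12) = 22.1% (one-sided) or 1 − 0.025^(1/12) = 26.5% (two-sided).

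These figures hold for any arm of that size. They show that recording would probably reveal a common problem and could not rule out an uncommon one. They do not estimate how often problems occur with this orthosis.

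**The case against.** The strongest reply is that this is an omission and an ambiguity, not a rule that conceals harm. Much of that reply stands.

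- **A reader might infer that the trial can show benefit but no harm.** The protocol does not support this. Respiratory rate, SpO2, chest wall ratio and CHOP INTEND can all worsen, and QUEST 2.0 touches on acceptability.
- **A reader might infer that the protocol orders intolerant children to be removed after randomisation.** It does not. The criterion sits with participant selection and has no timing. The protocol does not say that intolerance counts as poor adherence, nor that week-8 data are withheld from such children.
- **A reader might infer an established bias towards Group 2.** That needs both removal after randomisation and losses driven by intolerance, and neither is stated. The criterion also covers the exercises, which both groups do, so losses need not fall on one arm.
- **The design features are not an admission of respiratory risk.** The strap feature concerns movement, not breathing, and section 4 expects respiratory benefit.
- **The probabilities are generic.** Both the event rates and the 12 children in Group 2 are assumed.

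The reply does not remove the gap. No listed measure captures events between visits or in children who have left, and no section provides for recording them. What is recorded at visits is a protocol matter and cannot be left to a later analysis document. The orthosis part of the exclusion has no clear pre-randomisation meaning for a device that is first supplied after allocation.

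**Conclusion.** The point holds as a gap in data collection together with an undated criterion. Section 3.6 has no adverse-event or device-intolerance outcome, and its two assessment times miss problems between visits and in children who leave before week 8. The adherence exclusion could, on one plausible reading, remove children who cannot tolerate the orthosis before the only follow-up, and so could flatter Group 2 in the week-8 respiratory comparison. The direction of any bias depends on that reading and on losses being related to intolerance; its size cannot be computed from the protocol.

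For scale, the protocol's own allowance corresponds to about 3 to 4 children lost per arm under equal allocation. The detection probabilities of 72% and 93% are illustrative and rest on the assumed rates and arm size. The change should be made because it is cheap and because uncollected safety data cannot be reconstructed afterwards.

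**What to change.** 1. Add a safety outcome to section 3.6, recorded in both arms at the existing weekly supervision contact. It should cover skin problems, breathing difficulty, unplanned respiratory care, and any interruption of the orthosis or exercises with its reason.
2. Have the supervising staff complete it, not the outcome assessors, so that the blinding promised in section 3.4 is kept. For the same reason, do not add respiratory readings with the orthosis on and off in Group 2: they would reveal allocation to whoever takes them and have no Group 1 comparator.
3. Report the events descriptively by arm for all randomised children.
4. State in section 3.3 that the adherence criterion does not remove children after randomisation, and in section 3.6 that children who stop wearing the orthosis are still assessed at week 8.

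The cost is one short form at a contact that already takes place and one descriptive table, which means a little extra recording work. No visits or patients are added. The weekly contact is described as supervision of the exercises, so the staff who hold it need to be told what to record. No clinical stopping rule or wearing schedule is proposed.

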### **3.7. Sample Size Calculation**

A priori power analysis conducted using G\*Power 3.1 ( $f = 0.65$ ,  $\alpha = 0.05$ , power = 0.80) will indicate that a minimum of 18 participants (9 per group) will be required. Considering a potential dropout rate of 30%, 24 children will be recruited.

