### **3.8. Statistical Analysis**

SPSS version 25.0 will be used. Normality will be assessed using the Shapiro-Wilk test.

- Descriptive statistics: Mean  $\pm$  SD, median, and range.
- Group comparisons: Independent Samples t-test.
- Within-group comparisons: Paired Samples t-test.
- Effect size calculation: Cohen's d (small: 0.20-0.50, medium: 0.51-0.80, large:  $\geq 0.81$ ).
- Statistical significance:  $p < 0.05$ .

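### Section 3.7 claims 80% power with 18 children, but a two-sided reading of the planned t-test gives about 74% and needs 22 evaluable; the basis for 18 is not stated

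*Protocol*

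**What the plan says.** Protocol section 3.7 reports an "A priori power analysis conducted using G\*Power 3.1" with f = 0.65, alpha 0.05 and power 0.80, and concludes that "a minimum of 18 participants (9 per group) will be required". It continues: "Considering a potential dropout rate of 30%, 24 children will be recruited". It names no test family, sidedness or correlation between repeated measurements.

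Section 3.8 gives the between-group analysis as "Group comparisons: Independent Samples t-test", with paired t-tests within groups and significance at p < 0.05. Sidedness is not stated there either, and no ANOVA or repeated-measures model is listed. Results are to be expressed on a different effect scale from the one used for planning: "Effect size calculation: Cohen's d (small: 0.20-0.50, medium: 0.51-0.80, large" (0.81 or more).

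Section 3.6 fixes two measurement times: "Assessments will be conducted at baseline (pre-treatment) and after eight weeks of rehabilitation". The primary outcome is the Cobb angle on supine X-ray.

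**The concern.** The sample size and the analysis should describe the same test. Section 3.7 uses f, an ANOVA effect size, while section 3.8 plans a t-test. For two groups the two agree exactly once f is converted to d, so 18 can be checked directly against the planned test. On the usual two-sided reading it falls short.

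At stake is the meaning of the stated power. If the test is two-sided, the chance of missing a true difference of 1.3 SD with 18 evaluable children is about 26% (1 − 0.7355), not 20%. In a trial this small a non-significant Cobb-angle result is quite possible. A reader relying on 80% power would take it as stronger evidence against an orthosis effect than it is.

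**Working it through.** **Inputs.** From section 3.7: f = 0.65, alpha 0.05, target power 0.80, 9 per group, 24 recruited, 30% dropout. From section 3.8: independent t-test. From section 3.6: two measurement times. Assumptions: sidedness (both tried) and the correlation between the two times (range shown). Section 3.8 does not say whether week-8 values or changes are compared, so d is in SDs of whichever is used.

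**Effect size.** With two equal groups the group means lie half the difference either side of the overall mean, so f = d/2 and d = 2 × 0.65 = 1.30.

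**Planned t-test, two-sided.** Power comes from the noncentral t distribution with df = 2n − 2 and noncentrality d√(n/2). At n = 9 this is 1.30 × √4.5 = 2.758 on 16 df.

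| n per group | Total | Two-sided power | One-sided power |
|---|---|---|---|
| 8 | 16 | 0.677 | 0.796 |
| 9 | 18 | 0.7355 | 0.840 |
| 10 | 20 | 0.785 | 0.875 |
| 11 | 22 | 0.826 | 0.903 |
| 12 | 24 | 0.861 | 0.925 |

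A one-way ANOVA F-test with two groups gives the same values as the two-sided column. The smallest equal-group size reaching 80% two-sided is 11 per group, 22 in total.

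For unequal groups the noncentrality is d√(n₁n₂/(n₁+n₂)):
- 10/11 split: 1.30 × √(110/21) = 2.975, power 0.806, so 21 is enough.
- 8/9 split: 1.30 × √(72/17) = 2.675, power 0.706.

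For 80% two-sided power with 9 per group, d would have to be 1.41 (f = 0.70).

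**Reproducing the plan's 18.** Two routes return it.

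1. One-sided t-test: 8 per group gives 79.6% and 9 gives 84.0%, so the minimum is 18.
2. Repeated-measures ANOVA, between factors, two groups and two times: noncentrality f²·N·2/(1 + ρ) on 1 and N − 2 df. With ρ = 0.5 assumed, N = 16 gives 0.4225 × 16 × 2/1.5 = 9.01 and power 0.797. N = 18 gives 0.4225 × 18 × 2/1.5 = 10.14 and power 0.848. The minimum even N is 18 at each ρ tried from 0.50 to 0.70, 16 or fewer below that, and 20 or 22 above.

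The second route tests the group difference in the average of baseline and week 8. Baseline precedes treatment and cannot carry a treatment effect, so this is not the trial's question. The group-by-time interaction would address it, but does not return 18: with noncentrality f²·N·2/(1 − ρ) and ρ = 0.5, N = 8 gives 0.4225 × 8 × 2/0.5 = 13.52 and already 86% power.

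**At the planned recruitment.** 24 × 0.70 = 16.8, about 17 evaluable. Two-sided t-test power is 86% if all 24 are evaluable and about 71% with 17.

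**ANCOVA alternative.** Week-8 Cobb angle adjusted for baseline, 9 per group, a difference of 1.3 unadjusted SDs, two-sided 0.05. Simulation with 20,000 runs at ρ = 0.5 gives 0.821. If the covariate explains nothing, power with 18 is about 0.732 (noncentral F on 1 and 15 df). The assumed correlation therefore moves the figure from about 73% to about 82%, and higher above 0.5.

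**The case against.** The best defence is that the protocol states no sidedness, so 18 is not shown to be a miscalculation. The same t-test run one-sided needs exactly 9 per group, and section 4 expects a benefit in one direction. The use of f and the two time points fit the repeated-measures route, so 18 may be correct output from an undisclosed procedure. This part stands: a reader might infer that 18 is simply an arithmetic error, and the document does not support that. What it supports is an undisclosed basis that does not match section 3.8 as ordinarily read. A directional expectation does not specify a one-sided test, an unqualified p < 0.05 is conventionally two-sided, and neither route that returns 18 is written in the protocol. A SAP, not shown, could settle the sidedness. If it specified a one-sided test, 18 would follow.

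It can also be said that 24 children are recruited, and 24 evaluable give 86% two-sided. That is correct, but section 3.7 itself allows for 30% loss, which leaves about 17, below both 18 and 21.

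Because section 3.8 reports Cohen's d, a reader might also infer that 0.65 was really a d, with far lower power. The protocol writes f explicitly, and planning in f while reporting d is not an error. That reading is not supported.

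**Conclusion.** The point holds conditionally. If the t-test in section 3.8 is two-sided, section 3.7 overstates power at its own minimum by about 6 percentage points (about 74% against 80%), and the minimum should be 22 evaluable in equal groups, or 21 split 10/11. This rests on the protocol's f = 0.65, on d = 2f for equal groups, on the t-test's usual assumptions, and on the two-sided reading, which is conventional but unstated.

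Whatever the origin of 18, sections 3.7 and 3.8 need reconciling: the figure fits either a sidedness that is not declared or an analysis that is not planned and does not target the treatment effect. The gap is moderate, but the number is one the trial relies on and it is cheap to correct. A reader should not infer that 80% power for the unadjusted two-sided t-test survives the planned recruitment and dropout: about 17 evaluable gives about 71%.

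**What to change.** In section 3.7, name the test and its sidedness, give the effect as d = 1.30, and replace the claim for 18. Suggested text: for a two-sided independent t-test at 0.05 and d = 1.30, power is about 74% with 18 evaluable children, 83% with 22, 86% with 24, and about 71% with the roughly 17 expected if 30% of 24 are lost. State sidedness in section 3.8 as well.

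Alternatively, make a two-sided ANCOVA of week-8 Cobb angle adjusted for baseline the primary analysis in section 3.8, and quote power for that in section 3.7: about 82% with 18 evaluable for a difference of 1.3 unadjusted SDs if the baseline/week-8 correlation is 0.5. Mark the correlation as an assumption, and note that power is higher if it is higher and lower if it is lower or fewer than 18 are evaluable. This uses data already collected.

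Either change is a matter of a few sentences. The cost is a slightly less favourable stated power. Neither restores 80% for the unadjusted two-sided t-test: 22 evaluable after 30% loss would require 22/0.70 = 31.4, so 32 recruited.

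### Recruiting 24 children does not cover the assumed 30% dropout: about 17 would remain, below the protocol's own minimum of 18

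*Protocol*

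**What the plan says.** Section 3.7 (Sample Size Calculation) reports a G\*Power calculation with f = 0.65, α = 0.05 and power 0.80, and concludes that "a minimum of 18 participants (9 per group) will be required". The next sentence gives the allowance for loss and the recruitment target together: "Considering a potential dropout rate of 30%, 24 children will be recruited".

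The section does not state how 18 was inflated to 24, which G\*Power test was used, or whether the test is one- or two-sided. Section 3.8 lists "Group comparisons: Independent Samples t-test" with a 0.05 significance level, again without sidedness. No other section gives a different target, a different dropout rate, or a rule for replacing children who leave.

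**The concern.** An allowance for dropout should ensure that, if the assumed loss occurs, the number left still meets the requirement. Section 3.7 gives all three figures needed to check this (18, 30% and 24), and the check fails. Under the protocol's own assumption, the expected number of completers is below its own minimum.

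The first thing at stake is the statement itself. A reader would take it that the trial can lose 30% of its children and still have 18 to analyse, and it cannot. The second is some power. In a trial of 24, the margin is 6 losses, whereas 30% corresponds to about 7 (24 × 0.30 = 7.2).

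**Working it through.** **Inputs, all from section 3.7 unless noted.** Minimum 18 (9 per group); dropout 30%; recruitment 24; f = 0.65; α = 0.05. The t-test for the group comparison is from section 3.8. Assumptions added here: equal allocation (12 per group), d = 2f = 1.30 for two equal groups, and sidedness shown both ways.

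**Reproducing 24.** Multiplying by one plus the dropout rate gives 18 × (1 + 0.30) = 23.4, rounded up to 24. Per group, 9 × 1.30 = 11.7, rounded up to 12. This matches the stated figure.

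**What 24 leaves at 30% loss.** 24 × (1 − 0.30) = 16.8 in total, and 12 × 0.70 = 8.4 per group. Both are below the minimum (18 and 9).

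**What 30% loss implies.** The number recruited, times the proportion retained, must be at least 18: 18 / (1 − 0.30) = 25.7, so 26. Per group, 9 / 0.70 = 12.9, so 13. Check: 26 × 0.70 = 18.2.

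**What 24 does cover.** 1 − 18/24 = 0.25, that is, 6 losses.

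**Chance of reaching the minimum.** If each child leaves independently with probability 0.30, at least 18 of 24 complete with probability about 0.39. At least 9 complete in both groups of 12 with probability about 0.24 (0.4925² = 0.243). With 26 recruits, at least 18 complete with probability about 0.63.

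**Power attributable to the slip.** Noncentral t with d = 1.30, noncentrality d × √(n₁n₂ / (n₁ + n₂)) and n₁ + n₂ − 2 degrees of freedom:

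| Completers | Noncentrality | Two-sided 0.05 | One-sided 0.05 |
|---|---|---|---|
| 9 + 9 | 2.758 | 73.5% | 84.0% |
| 8 + 9 | 2.675 | 70.6% | 81.8% |
| 8 + 8 | 2.600 | 67.7% | 79.6% |

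Measured from the protocol's own minimum of 9+9, the loss is 2.9 to 5.8 percentage points two-sided, or 2.2 to 4.4 points one-sided.

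**A further setting that reproduces 18.** A repeated-measures between-factors F test with f = 0.65 and two measurements also gives 18 if the correlation between measurements is assumed to be 0.5 or 0.7. At 0.5, power is 84.8%, 82.4% and 79.7% for 18, 17 and 16 children. At 0.7 it is 80.2%, 77.5% and 74.6%. The loss is again about 2 to 6 points.

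**The case against.** The strongest reply is about size. The target is two children short, the expected shortfall at 30% loss is about one completer (18 − 16.8 = 1.2), and the protocol calls 30% only a potential rate. Under settings that reproduce 18, power at 16 or 17 completers stays close to or above 80% in most cases. This is a small single-centre trial in a rare disease, and no outcome or test is affected. All of this stands and limits the weight of the point. It does not remove the contradiction, because 16.8 is below 18 whichever test or sidedness is assumed.

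Two stronger readings are tempting. The first sets 68% to 71% power against the stated 80% and attributes the whole gap to dropout. The documents do not support that. On the same two-sided t-test the stated minimum of 9+9 already gives 73.5%, so most or about half of that gap comes from the base figure of 18, which is a separate question. A two-sided test is a reasonable reading of section 3.8, but neither section fixes it.

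The second states as fact that 24 came from multiplying by 1.3. The match is exact after rounding, but section 3.7 gives no formula. The number is also 12 per group and a multiple of the six strata in section 3.4, so it could have been chosen for convenience.

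**Conclusion.** The point holds. The three figures in section 3.7 are inconsistent: at the assumed 30% dropout, 24 recruits leave about 17 children against a required 18. A 30% rate implies 26, and 24 covers no more than 25%. This part rests only on the protocol's own numbers.

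The consequence for power is modest, about 2 to 6 percentage points relative to 9+9. That size depends on assumptions that the protocol does not settle: d = 1.30 from f = 0.65, the test used in the calculation, and its sidedness. It is a definite error in a stated figure and should be corrected, but it does not invalidate the trial.

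**What to change.** Keep 24 and restate what it covers, for example:

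> *24 children allow for up to 25% dropout while retaining 18; at 30% dropout about 17 would remain, below the minimum of 18.*

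Add that a planning rate of 30% would imply 26. No additional enrolment is needed for the statement to be correct.

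Do not write a power figure into this sentence. Doing so would settle the unstated test and sidedness within a dropout correction, and could set a figure near 70% beside an unrevised claim of 80% at 18. The power of the base figure should be corrected separately.

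The cost is one sentence and a stated dropout tolerance that is slightly less favourable.
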